### **8.5.3 Analysis of Secondary Endpoints**

All secondary endpoints will be performed at a significance level of 5% two-sided.

The analysis of the overall palatability will be described as secondary at time t2-5min.

### **8.5.4 Analysis of Safety and Other Endpoints**

A treatment-emergent AE is any AE temporally associated with the use of study treatment, with onset date on or after initiation of study treatment until End of Day 2.

AEs will be coded using the MedDRA coding dictionary. All AEs will be displayed in subject listings. AEs will be categorized and tabulated by System Organ Class, Preferred Term, severity and relationship to IMP. Additionally listings of SAEs will be generated.

In the summary tables of subjects, if a subject has more than one occurrence of an AE for a specific Preferred Term, he/she will be counted only once for that preferred term. In the summary tables, the most severe occurrence of an AE, as well as the most extreme relationship

of the AE to the study treatment, will be indicated in cases of multiple occurrences of the same AE.

Adverse events summary will be displayed by treatment group for the following categories:

- All AEs
- Treatment-emergent adverse events
- Treatment emergent Serious adverse events
- Adverse events leading to study discontinuation

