### **6.5.5 Management of Specific Adverse Events or Adverse Drug Reactions**

As this is a Swill and Spit study, no safety or tolerability concerns are expected (drug not swallowed). Even in case of inadvertent swallowing of a 150 mg tablet or in case of unexpected high buccal absorption, safety concerns should not be raised since the 150 mg ODT dose is under the used therapeutic dose of 40 mg/kg rac-PZQ (7 rac-PZQ ODTs or 3 L-PZQ ODTs needed to treat a 25 kg 6 year old child).

Children are kept under observation for least 2 hour after the last taste assessment before leaving the unit. Spontaneously reported adverse events (by parents/guardians) will be managed in the participating health facility by study medical doctor who will remain in the facility during the trial and two weeks thereafter. AEs will be recorded in the CRF until one week after the last taste assessment.

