## **7.4 Assessment of Safety**

The safety profile of the IMP will be assessed through checking, baseline medical conditions, adverse events (AEs) and physical examination observations.

The investigator will report any AEs, whether observed by the Investigator or reported by the subject (see Section 7.8.1.2). The reporting period for AEs is from ICF signature until subject discharge at Day 2. Spontaneously reported adverse events (by parents/guardian) will be recorded in the CRF until one week after the last taste assessment.

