### **7.4.1.3 Definition of the Adverse Event Reporting Period**

The AE reporting period for safety surveillance begins when the subject is initially included in the trial (date of signature of informed consent) and continues until the visit of Day 2.

Any SAE assessed as related to the used IMPs must be reported whenever it occurs, irrespective of the time elapsed since the last administration of the IMP.

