### **7.4.1.4 Procedure for Reporting Serious Adverse Events**

#### **Serious Adverse Events**

In the event of any new SAE occurring during the reporting period, the Investigator must immediately (within a maximum of 24 HOURS after becoming aware of the event) inform the Sponsor or its designee and the Safety Monitoring Committee in writing.

All written reports should be transmitted using the SAE Report Form, which must be completed by the Investigator following specific completion instructions.

In exceptional circumstances, an SAE (or follow-up information) may be reported by telephone; In these cases, a written report must be sent immediately thereafter by fax or e-mail. Names, addresses, and telephone and fax numbers for SAE reporting will be included in the trial-specific SAE Report Form and other instructions.

Relevant pages from the CRF may be provided in parallel (for example, medical history, concomitant drugs). Additional documents may be provided by the Investigator, if available (for example, laboratory results, hospital report and autopsy report). In all cases, the information provided on the SAE Report Form must be consistent with the data about the event recorded in the CRF.

The Investigator must respond to any request for follow-up information (for example, additional information, outcome, final evaluation, other records where needed) or to any question the Sponsor/designee may have on the AE within the same timelines as those noted above for initial reports. This is necessary to ensure prompt assessment of the event by the Sponsor or designee and (as applicable) to allow the Sponsor to meet strict regulatory timelines associated with expedited safety reporting obligations. Requests for follow-up will usually be made via the responsible Monitor, although in exceptional circumstances the Global Drug Safety department may contact the Investigator directly to obtain further information or to discuss the event.

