#### **7.4.1.5 Safety Reporting to Health Authorities, Independent Ethics Committees/ Institutional Review Boards and Investigators**

The Investigator will send appropriate safety notifications to Health Authorities in accordance with applicable laws and regulations.

The Investigator must comply with any applicable site-specific requirements related to the reporting of SAEs (particularly deaths) involving trial subjects to the IEC/IRB that approved the trial.

In accordance with ICH GCP, the Sponsor/designee will inform the Investigator of “findings that could adversely affect the safety of subjects, impact the conduct of the trial or alter the IEC’s/IRB’s approval/favorable opinion to continue the trial.” In particular and in line with respective regulations, the Sponsor/designee will inform the Investigator of AEs that are both serious and unexpected and are considered to be related to the administered product (“suspected unexpected serious adverse reactions” or SUSARs). The Investigator should place copies of Safety Reports in the Investigator Site File. National regulations with regard to Safety Report notifications to Investigators will be taken into account.

All SAEs that are related to study participation (e.g. procedures, a change from existing therapy) or are related to a concurrent medication will be recorded from ICF signature until discharge

All SAE reports and/or all SAE participants-related safety information should be sent to Merck Serono Global Drug Safety Department:

[contact]

[contact]

[contact]

The SAE will be summarized and reported to IRBs by the PI in the required time frame as specified by the IRB. The PI and/or the Sponsor will report the SAE to TFDA.

A written report of the SAE by the study site will be submitted within 24 hours for fatal and life threatening SAEs by phone, followed by paper reports within 7 calendar days of the investigator becoming aware of the SAE on the sponsor SAE report form, containing the minimal required information. All other cases should be reported within 14 days in order to comply with regulations mandating sponsor notification of specified SAEs to TFDA within 7 calendar days

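### Sections 7.4.1.4 and 7.4.1.5 give incompatible SAE reporting times, and the one-week AE recording period does not match the Day 2 limits in 7.4.1.3 and 8.5.4

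*Protocol*

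**What the plan says.** **SAE reporting times.** Protocol section 7.4.1.4 covers any new SAE in the reporting period. The investigator informs the sponsor or its designee and the Safety Monitoring Committee in writing, "within a maximum of 24 HOURS after becoming aware of the event". Telephone is for exceptional circumstances and must be followed at once by a written report.

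Section 7.4.1.5 gives other times. For fatal and life-threatening SAEs the site phones within 24 hours and sends paper on the sponsor's SAE form within 7 calendar days of becoming aware. Any SAE outside that class "should be reported within 14 days in order to comply with regulations mandating sponsor notification of specified SAEs to TFDA within 7 calendar days".

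**AE windows.** Section 6.5.5 says that "AEs will be recorded in the CRF until one week after the last taste assessment". Section 7.4 is narrower. It states that "The reporting period for AEs is from ICF signature until subject discharge at Day 2", and then adds: "Spontaneously reported adverse events (by parents/guardian) will be recorded in the CRF until one week after the last taste assessment". Section 7.4.1.3, the formal definition, says that the period "continues until the visit of Day 2" and does not mention the extra week. It does add that an SAE judged related to the products "must be reported whenever it occurs, irrespective of the time elapsed since the last administration of the IMP". Section 7.4.1.6 assesses AEs for final outcome at Day 2. Section 8.5.4 defines a treatment-emergent AE as one "with onset date on or after initiation of study treatment until End of Day 2".

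**The concern.** The first problem is one of conduct. Two adjacent subsections tell the same site, about the same events and on the same sponsor form, to report on different clocks. Staff who follow 7.4.1.5 alone can breach 7.4.1.4 without knowing it. The 14-day allowance is also justified by a 7-day duty, which a report at the limit could not serve. The subjects are children aged 6 to 11, so the instruction should not be ambiguous.

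The second problem is one of definition. The protocol collects some events for a week after the last taste, and it accepts that a related SAE may appear at any later time. Its treatment-emergent definition stops on the day of the last taste. A related event starting on Day 3 is therefore recordable, and reportable if serious, but it is barred from the two summaries meant to show events that emerge on treatment.

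**Working it through.** The protocol states no figure to reproduce. The check sets the sections side by side and counts days.

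**SAE clocks**

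| SAE class | Section 7.4.1.4 | Section 7.4.1.5 |
|---|---|---|
| Fatal or life-threatening | written, 24 hours | phone, 24 hours; paper, 7 calendar days |
| All other | written, 24 hours | 14 days |
| Duty that the 14 days are said to serve | – | 7 calendar days |

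The clocks in 7.4.1.4 and in the 7-day paper rule start at the investigator's awareness. The sentence with the 14-day limit does not say when the 14 days or the authority's 7 days start. I assume that all of them start at awareness. Then:

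- Other SAEs, written report: 14 − 1 = 13 days after the limit in 7.4.1.4.
- Other SAEs, against the notification: 14 − 7 = 7 days after it is due.
- Fatal or life-threatening SAEs, written report: 7 − 1 = 6 days after the limit in 7.4.1.4, although a phone report has been made.

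If the authority's clock started only when the sponsor received the report, the second difference would disappear. The stated purpose would then make no sense, because a site deadline could not help the sponsor meet a clock that had not started. The differences against 7.4.1.4 remain.

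**AE windows**

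The last taste is on Day 2, so recording ends on about Day 2 + 7 = Day 9.

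| Section | End of window |
|---|---|
| 6.5.5 | about Day 9 |
| 7.4, reporting period | Day 2 discharge |
| 7.4, spontaneous parent or guardian reports | about Day 9 |
| 7.4.1.3 | Day 2 visit (no limit for related SAEs) |
| 7.4.1.6, final AE outcome | Day 2 |
| 8.5.4, treatment-emergent | end of Day 2 |

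Days with recording but outside the treatment-emergent window: Days 3 to 9, which is 9 − 3 + 1 = 7 of the roughly 9 days from first taste.

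**Where a Day 3 to 9 event appears.** Section 8.5.4 names four summaries by treatment group. The event enters the all-AE summary. It cannot enter the treatment-emergent AE or treatment-emergent SAE summary. The fourth, AEs leading to discontinuation, does not depend on the window. The event also stays in the subject listings and in the tabulation by relationship to product, and an SAE stays in the SAE listing.

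**The case against.** **On the SAE clocks.** Section 7.4.1.5 is headed as reporting to authorities, ethics committees and investigators. The 14-day sentence follows sentences about the ethics boards and the national authority, so it may describe an additional route that leaves the 24-hour rule in force. The specified SAEs with a 7-day notification may also be only the fatal and life-threatening ones. Both readings are possible, and a site that obeys 7.4.1.4 in every case reports nothing late. But the text supports neither outright. It speaks of site reports on the sponsor's own form, it ties the 14 days for all other cases to the 7-day duty, and it does not define which SAEs are specified.

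**On the AE windows.** This objection carries more weight. Section 7.4 limits the extra week to spontaneous reports, and the sentence in 6.5.5 follows one about such reports, so it can be read in the same way. Children and parents are questioned on the two visit days (7.4.1.2), and the Day 2 examination is the end-of-study assessment (7.1.3). Ending treatment-emergent status where active questioning ends is a defensible choice. After Day 2 a child has tasted all five preparations, so a late event cannot be cleanly assigned to one treatment group. What remains is that 7.4.1.3 omits the week, the sentence in 6.5.5 carries no limit of its own, and the plan does not say how events from that week are treated beyond the all-AE summary and the listings.

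**Stronger readings to avoid.** A reader might infer that late reactions disappear from the safety results. They do not, because the all-AE summary, the relationship tabulation and the listings keep them. Nor does the protocol call the treatment-emergent tables its main safety output. A reader might also infer that all AEs are actively collected to Day 9, or that the treatment-emergent window ought to be seven days. Section 7.4 contradicts the first, and nothing in the protocol fixes the second.

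**Conclusion.** The SAE conflict holds as written and is the main point: 24 hours in 7.4.1.4 against 7 or 14 days in 7.4.1.5, a difference of up to 13 days, with a 14-day allowance justified by a 7-day duty. The size assumes that the clocks start together at awareness and that a site acts on 7.4.1.5 alone. It is a risk of late reporting, not evidence that any report would be late.

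The AE-window point holds in a narrower form and is secondary. Events starting on about Days 3 to 9 are recorded and displayed, but two of the four AE summaries exclude them by rule, whatever their judged relationship. The protocol expects no safety concerns in a swill-and-spit study, so the number affected is probably small.

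Neither part touches the primary VAS analysis. Both should be corrected because the wording affects safety reporting and is cheap to change. The protocol does not show which deadline or window is the intended one.

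**What to change.** 1. Reconcile sections 7.4.1.4 and 7.4.1.5 so that the site-to-sponsor times agree for each class of SAE. State when each clock starts, who receives each report, and which SAEs are the specified ones. No allowed site interval should exceed the notification that it serves.
2. Reconcile sections 6.5.5, 7.4, 7.4.1.3, 7.4.1.6 and 8.5.4. Either make the recording period and the treatment-emergent definition agree, or keep the Day 2 limit and state that spontaneous AEs with onset after Day 2 are summarised separately. In both cases 7.4.1.3 should mention the one-week recording, and 6.5.5 should say whether it covers only spontaneous reports.

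The cost is protocol wording, carried through to any analysis plan and reporting instructions that repeat it. No new data, visits or subjects are needed.

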**Reference IMP: dose/mode of administration/dosing schedule:**

Current PZQ tablets (Cesol 600 mg)

**Mode of administration:** The tablet will be crushed and dispersed in water and ¼ of this dispersion (containing 150 mg), will be administered in the mouth cavity but not swallowed. .

**Planned trial and treatment duration per subject:** One treatment period of 2 days and a screening period of up to 14 days results in up to 3 weeks per subject.

The study is a two period, single blind cross-over design on Day 1 and a three period single blind cross-over on Day 2. The palatability assessments on Day 1 will involve the auto-disintegration of ODTs that will be put and disperse themselves in the mouth cavity to be followed by spit of the dispersed tablet. On Day 2, the swill and spit of the solutions made from both tablets in water

will take place. In addition to the tasting of the Rac-PZQ ODT and L-PZQ ODT on Day 2, the current Praziquantel tablets will be crushed and then dispersed in water for similar tasting & spitting thereof. The schedule of assessment is detailed in Table 1 below.

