## Events Not to Be Considered as AEs/SAEs

Medical conditions present at the initial trial visit that do not worsen in severity or frequency during the trial are defined as Baseline Medical Conditions, and are not to be considered AEs.

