### 7.4.1.2            Methods of Recording and Assessing Adverse Events

On both visit days, the subject and the parents / representatives will be queried on changes in his or her condition by questioning. During the reporting period, any unfavorable changes in the subject's condition will be recorded as AEs, whether reported by the subject or observed by the investigator.

Complete, accurate and consistent data on all AEs experienced for the duration of the reporting period (defined below) will be reported on an ongoing basis in the appropriate section of the CRF. All SAEs must be additionally documented and reported using the appropriate Serious Adverse Event Report Form as described in Section 7.4.1.4

It is important that each AE report include a description of the event, its duration (onset and resolution dates and times, its severity, its causal relationship with the trial treatment, any other potential causal factors, any treatment given or other action taken, and its outcome. In addition, serious cases should be identified and the appropriate seriousness criteria documented.

Specific guidance can be found in the CRF Completion and Monitoring Conventions provided by the project management.

An AE monitoring and reporting system for this study will be implemented according to study specific instructions developed based on this protocol.

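### Treatment-emergent AEs are defined by onset date alone, so an AE that starts after consent and worsens after tasting can miss the two treatment-emergent tables

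*Protocol*

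**What the plan says.** Section 8.5.4 defines a treatment-emergent AE as one linked in time to study treatment, "with onset date on or after initiation of study treatment until End of Day 2". It then lists four AE summaries by treatment group: all AEs, treatment-emergent AEs, "Treatment emergent Serious adverse events", and AEs leading to discontinuation. It also requires subject listings of every AE and separate SAE listings.

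Collection starts earlier than that window. Section 7.4 states: "The reporting period for AEs is from ICF signature until subject discharge at Day 2". Section 7.4.1.3 likewise starts the period at the date of informed consent. The Synopsis gives the length of the two phases: "One treatment period of 2 days and a screening period of up to 14 days".

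Worsening is addressed in Section 7.4.1.1, under the heading on events not considered AEs or SAEs. Conditions "present at the initial trial visit that do not worsen in severity or frequency during the trial" are baseline medical conditions and are not AEs. On recording, Section 7.4.1.2 says that during the reporting period "any unfavorable changes in the subject's condition will be recorded as AEs", and it refers to CRF completion conventions for further guidance.

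**The concern.** A treatment-emergent definition normally covers events that begin after the first dose and events that were already present but got worse after it. Section 8.5.4 has only the first part. The protocol itself treats worsening as meaningful in Section 7.4.1.1, but only for conditions present at the initial trial visit.

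That leaves a narrow group uncovered: complaints that arise between the initial visit and the first tasting, continue into the tasting days, and then become more severe or serious. A mild cough or mild abdominal pain beginning a few days before Day 1 is an example. Aggravation of such a complaint after a product is put in the mouth is something the treatment-emergent tables are meant to show. Read literally, the rule omits it, and an omission can only lower the treatment-emergent count.

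**Working it through.** The protocol gives no figure to reproduce. The check applies the stated rule to each type of event.

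**Inputs**
- AE collection: from consent to discharge on Day 2 (Sections 7.4 and 7.4.1.3).
- Screening: up to 14 days; treatment: 2 days (Synopsis).
- Treatment-emergent rule: onset date on or after initiation of treatment, until End of Day 2 (Section 8.5.4).

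**Applying the rule**
1. *New complaint after the first tasting, by End of Day 2.* The onset date is inside the window, so it is counted.
2. *Condition present at the initial visit that worsens after a tasting.* Under Section 7.4.1.1 it is not an AE until it worsens. The worsening is the AE, and its natural onset is the date of worsening. It is counted.
3. *Complaint that begins on Day 1 before the first tasting.* The rule uses onset date. If dates alone are compared, the event shares the date of first treatment and is counted, whether or not it worsens.
4. *Complaint that begins after the initial visit, on a date before Day 1, and worsens or becomes serious after a tasting.* It is already an AE with a pre-treatment onset date. It fails the rule and is absent from both treatment-emergent tables, unless the worsening is a separate record with its own onset date.

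Only case 4 is a gap.

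**Does the recording rule close it?** Section 7.4.1.2 requires unfavourable changes to be recorded as AEs. It asks each AE report for onset and resolution dates and a severity. It does not say that worsening of an AE already on file opens a new record with a new onset date. The sentence in Section 8.5.4 on multiple occurrences governs counting within a Preferred Term and the severity shown. It assigns no onset date.

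**Where a case 4 event would still appear.** In the summary of all AEs, in the subject listings and, if serious, in the SAE listings.

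**Scale.** With 48 children, one omitted child is 1/48 = 2.1 percentage points. That is the arithmetic of any single missed event in a group of 48. It does not estimate how many events this rule would omit, and the protocol gives no basis for that number.

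**The case against.** The strongest reply is that Section 7.4.1.2 already solves the problem. A mild cough that becomes moderate after a tasting is an unfavourable change, child and parents are questioned on both days, and the change would naturally be recorded as an AE dated to that change. Date handling for worsened events may also be settled in the CRF conventions or the SAP, which are not at hand. This is a fair reading and it may be how the site works. It does not dispose of the point, because Section 8.5.4 itself states the definition, states it by onset date alone, and nothing in the protocol makes a new record mandatory.

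The remaining objections succeed in limiting the point:
- A reader might infer that such events vanish from the safety report and that the products would look safer than they are. The protocol does not support that, since three other outputs would carry the event. SAEs also go to the sponsor and the Safety Monitoring Committee within 24 hours (Section 7.4.1.4).
- A reader might extend the gap to worsening baseline conditions. Section 7.4.1.1 makes that worsening the AE itself, so it falls inside the window.
- A reader might picture a mild wheeze turning into bronchospasm. That is a poor illustration. Exclusion 10 names bronchospastic disease, subject to the investigator's opinion, and eligibility is rechecked on Day 1. Milder complaints could still pass, because the definition of significant illness in exclusion 9 rests on fever, raised respiratory and heart rates and severe oral thrush.

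**Conclusion.** The point holds in a limited form. As written, Section 8.5.4 leaves out of the treatment-emergent AE and SAE summaries an AE that begins after the initial visit, on a date before the first tasting, and worsens or becomes serious after a tasting. This assumes that the worsening is kept within the existing AE record; if it is entered as a new AE, the event is counted.

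The effect is confined to two summary tables. Few children are likely to be involved, given the health exclusions, the Day 1 recheck and two days of tasting with the product spat out. Any specific count would be an assumption. No hypothesis or decision rule in the protocol uses these counts, and the palatability endpoints are unaffected. Severity: minor. It is still worth correcting, because the rule as stated is too narrow, sits awkwardly with Section 7.4.1.1, and is cheap to change.

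**What to change.** In Section 8.5.4, define a treatment-emergent AE or SAE as one that first occurs, worsens in severity or becomes serious on or after the first tasting until End of Day 2. Classify a worsened event by its date of worsening. This carries the worsening principle of Section 7.4.1.1 through to the analysis.

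Add one CRF completion note on how worsening of an existing AE is recorded, so that the date is available. No extra visits, assessments or children are needed. The treatment-emergent count may come out slightly less favourable.
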